##### Experience sampling data

ESM data will be gathered via NiceDay in the experimental condition. At three random moments per day, participants will be asked to register their emotional states. Participants will be asked to register their compulsions in the app throughout the day. Furthermore, participants can use the dairy option to plan activities, such as exposure exercises. The data collected with NiceDay will be used as an indirect measure to assess patients’ motivation, self-efficacy, and adherence to the treatment, by, for example, the number of registrations, how often a patient takes initiative to plan activities. Participants in the experimental condition will be invited to fill out experience sampling data during the active treatment phase of 20 weeks.

#### Mediation variables

We will be using the following measures to assess for a possible mediating role on treatment effect.

##### The Self-Efficacy Questionnaire for OCD (SEQ-OCD)

In order to measure patient’s self-efficacy regarding their OCD symptoms, we adapted the self-efficacy questionnaire for phobic situations (SEQ-PS). The SEQ-PS is a 13-item psychometric scale that is designed to measure the perceived ability to cope with phobic symptoms when approaching feared stimuli [36]. Responses are recorded on a 5-point scale. The SEQ-SP was found to have Cronbach’s alpha of 0.94. We adapted the SEQ-PS to measure symptoms of OCD when being confronted with the object of intrusions and not being able to perform compulsions. The SEQ-OCD will be included in all measurement moments.

##### The Acceptance and Action Questionnaire II (AAQ-II)

The AAQ-II [37] is a 7-item measure of psychological inflexibility/experiential avoidance. Answers are given on a 7-point scale ranging from 1 = never true to 7 = always true. The Dutch translation of the AAQ-II has been found to have good psychometric properties [38]. Experiential avoidance has been found to play some role in the development of obsessive–compulsive symptoms but it remains yet unclear to what extent [15, 18, 19]. We included the AAQ-II to assess the possible role on symptom severity and treatment effect. The AAQ-II will be included in all measurement moments.

#### Control variables

We will be using the following measures to control for a possible influence on treatment effect.

##### Technology Acceptance Questionnaire (TAQ-NL)

We will use a technology acceptance questionnaire (TAQ-NL) to assess whether acceptance of the NiceDay application influences treatment outcome in the intervention group. The TAQ is adapted from the Technology Acceptance Model and extended with constructs from the Unified theory of Acceptance and Use of Technology [39]. Constructs of the questionnaire include intention of use, perceived ease of use, perceived usefulness, and several organization context factors (i.e., facilitating conditions, subjective norm). The TAQ-NL was pilot tested and is currently being validated in a Dutch sample [40]. The items are presented in statements which will be rated on a 5-point Likert scale ranging from 1 = “strongly disagree” to 5 = “strongly agree”. The TAQ-NL will be administered to participants at posttest.

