Furthermore, we will be assessing possible predictors and mediators of treatment effect. Experiential avoidance, the avoidance of unpleasant inner experiences such as fear, discomfort and bodily sensations is found to play a crucial role in the development and maintenance of obsessive–compulsive symptoms [15–19]. Also, meta-analysis showed that this effect differed between the different subtypes of OCD, patients with the focus on obsessions and responsibility for harm seem to benefit more from a reduction in experiential avoidance [17]. Therefore, we will examine the possible effect of experiential avoidance as a predictor for treatment outcome and investigate if this differs between subgroups of patients. Also, self-efficacy, someone’s belief in his or her capacity to perform actions necessary to attain certain goals, has found to be positively correlated with symptom severity in OCD [20, 21]. Moreover, self-efficacy was found to have a mediating role in the treatment of OCS [22]. Since our experimental condition appeals to patients’ own contribution in their treatment approach, we aim to investigate if there is a difference in the increase of self-efficacy between conditions and if self-efficacy works as a mediating factor on treatment effect.

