##### The eHealth Literacy Questionnaire (eHLQ)

To determine whether eHealth Literacy influences treatment effect in the intervention group, we will use the eHealth Literacy Questionnaire. The eHealth Literacy Questionnaire (eHLQ) aims to measure eHealth literacy based on the 7-dimensional eHealth Literacy Framework [41]. The eHLQ consist of 35 items that are scores on a 7-scale answers scale. It consists of 7 scales, namely; using technology to process health information, understanding of health concepts and language, ability to actively engage with digital services, feel safe and in control, motivated to engage with digital services, access to digital services that work and digital services that suit individual needs. The eHLQ was found to have good psychometric abilities [41].

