## Data collection and management

### Plans for assessment and collection of outcomes {18a}

In our study, we will administer a combination of structured clinical interviews and self-report questionnaires. Clinical interviews will be administered by trained outcome assessors. Outcomes of the questionnaires will be collected through the software package Research Manager and stored in encrypted form on a secured server. Measurement moments will be at baseline, 5 weeks of treatment, 10 weeks of treatment (midtest), 15 weeks of treatment, 20 weeks of treatment (posttest), 6 weeks follow-up, 3 months follow-up, 6 months follow-up, and 12 months follow-up. Primary and mediation outcomes will be measured at all measurement moments. Secondary outcomes will be measured at baseline, midtest, posttest, and in all follow-up moments. Control variables will be measured at baseline. For more information on outcomes, see {12}.

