## Statistical methods

### Statistical methods for primary and secondary outcomes {20a}

#### Primary outcomes

Multilevel mixed modelling analysis will be used to investigate differences in treatment effect, measured through symptom reduction on the Y-BOCS. Multilevel analysis is especially suitable to analyze repeated measurement data because it takes into account the dependencies among observations nested within individuals. Another advantage of this methodology is its ability to handle missing data. We will start with a three-level structure with treatment effect (Y-BOCS score) as dependent variable, repeated measures at the first, individuals at the second, and treatment condition at the third level. We will then add age, gender, Ehealth literacy scale scores, and medication use to the model as covariates. We will determine the covariance structure empirically. Effect sizes and clinical significant change according to the Jacobson and Truax criteria will be calculated to estimate respectively the magnitude of the treatment effect and the significance of the results for clinical practice [49]. All analyses will be done both according to the intention-to-treat principle and per protocol in order to gain as much insight as possible into the efficacy of the intervention, as recommended by CONSORT.

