### Methods for additional analyses (e.g., subgroup analyses) {20b}

Non applicable, no additional analyses are planned.

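### The eHealth literacy question needs an interaction that the stated models do not contain; the timing of the TAQ-NL and the experiential-avoidance subgroup question also need reconciling

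*Protocol article*

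**What the plan says.** Under Outcomes {12}, the heading Control variables covers two instruments, the TAQ-NL and the eHLQ, with a shared purpose: "We will be using the following measures to control for a possible influence on treatment effect".

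- **eHLQ.** Its own section sets the question: "To determine whether eHealth Literacy influences treatment effect in the intervention group, we will use the eHealth Literacy Questionnaire". The primary-outcome methods in {20a} then say: "We will then add age, gender, Ehealth literacy scale scores, and medication use to the model as covariates". The secondary-outcome methods list the same covariates.
- **TAQ-NL.** It is collected "to assess whether acceptance of the NiceDay application influences treatment outcome in the intervention group". On timing, its section says "The TAQ-NL will be administered to participants at posttest", whereas Plans for assessment and collection of outcomes {18a} says "Control variables will be measured at baseline" and names no exception. TAQ-NL appears in none of the models in {20a}.
- **Experiential avoidance.** Background and rationale {6a} announces: "we will examine the possible effect of experiential avoidance as a predictor for treatment outcome and investigate if this differs between subgroups of patients".
- **Additional analyses.** Section {20b} reads: "Non applicable, no additional analyses are planned".

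**The concern.** A question about whether a patient characteristic changes a treatment effect is answered by comparing its association with outcome between the arms. A covariate entered once for both arms estimates a single association and adjusts the treatment contrast for it. The trial could therefore collect eHLQ from every participant, fit the stated models and still have no estimate that answers its own question. The risk is that the covariate coefficient is then reported as though it did.

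The TAQ-NL conflict matters because the two time points give different measurements. Acceptance of an app before use is an expectation; after 20 weeks it is a judgement formed during treatment. At posttest it is taken at the same visit that closes the primary outcome window (Y-BOCS, baseline to posttest), so it may partly reflect how well treatment went.

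The experiential-avoidance subgroup question is announced in one section and excluded by another, so a later subgroup result would have no planned status.

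**Working it through.** The article gives no figure on this point, so there is none to reproduce. The check sets the sections side by side and illustrates the eHLQ part with assumed slopes.

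**1. What the covariate coefficient estimates.** Let b0 and b1 be the slopes of outcome on standardized eHLQ in the control and app arms. With 1:1 allocation (Sequence generation {16a}) and the same eHLQ spread in both arms:

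- covariate-only model: coefficient = (b0 + b1) / 2
- model with eHLQ-by-treatment term: interaction = b1 - b0

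Three assumed cases were simulated with 80 per arm (160 / 2), one outcome per patient, residual SD 1 and 3000 runs:

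| b0 / b1 | (b0 + b1)/2 | simulated covariate coefficient | b1 - b0 | simulated interaction | interaction significant at 5% |
|---|---|---|---|---|---|
| -0.2 / -0.2 | -0.2 | -0.198 | 0 | 0.002 | 5.3% |
| 0 / -0.4 | -0.2 | -0.203 | -0.4 | -0.406 | 70.5% |
| +0.2 / -0.2 | 0 | 0.002 | -0.4 | -0.399 | 70.2% |

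Rows 1 and 2 cannot be told apart by the covariate coefficient, although literacy modifies the effect in only one of them. In row 3 the coefficient is near zero despite clear modification.

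**2. A model in the app arm alone.** The eHLQ wording could also mean an association within that arm. No such model is listed. It would not isolate effect modification either: rows 1 and 3 share the app-arm slope of -0.2 but have interactions of 0 and -0.4.

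**3. Power of the repair.** Fisher z, two-sided alpha 0.05, power 0.80, n = 80 per arm with complete data (an assumption):

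- within one arm: r = tanh[(1.960 + 0.842) / √77] = tanh(0.319) = 0.31
- between arms, with correlation 0 in the other arm: r = tanh[(1.960 + 0.842) × √(2/77)] = tanh(0.452) = 0.42

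Only a fairly strong modification would be detected reliably.

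**4. TAQ-NL timing.** It is a control variable by its heading, collected at posttest by its own section and at baseline by the general rule in {18a}. These cannot all hold. The eHLQ section gives no time, so the {18a} rule places it at baseline without conflict, which suits a moderator.

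**5. Experiential avoidance.** The mediation section in {20a} covers group differences in SEQ-OCD and AAQ-II and a bootstrapped mediation analysis. It contains no predictor-by-subgroup analysis, and {20b} plans nothing more.

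**The case against.** The article condenses a fuller plan. Its model description does not even name a treatment-by-time term, so silence on an eHLQ interaction is weak evidence that one is excluded; interactions are often left to the SAP. It is true that main-effect-only entry is inferred from the word covariates. But {20b} does not defer to another document. It says that nothing further is planned, and that statement cannot stand beside the eHLQ question.

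Posttest is also a sensible time to ask about ease of use and usefulness of an app, and the conflict sets a specific statement against a one-line general rule. The schedule figures are not shown here and may settle it. This makes the repair a matter of wording, but the two sections still disagree.

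A reader might go further on TAQ-NL in three ways that the documents do not support:

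- *That the trial will adjust its treatment effect for a post-treatment variable.* No listed model includes TAQ-NL; only the general sentence under Control variables points that way.
- *That any association with outcome would be reverse causation.* This is plausible, but the article gives no correlation between improvement and acceptance, so neither its presence nor its size can be stated.
- *That a posttest TAQ-NL is useless.* Y-BOCS is also measured at four follow-ups after posttest, and the score precedes those.

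**Conclusion.** The point holds for eHLQ: the stated models cannot answer the stated question, and the article says no other analysis is planned. This follows from what a common coefficient estimates and does not depend on the assumed slopes, which only illustrate it. It does rest on reading covariates as main effects.

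The TAQ-NL timing is a plain contradiction between two sections. If posttest stands, the score should not be read as influencing the baseline-to-posttest change. The experiential-avoidance subgroup question conflicts with {20b}.

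All three concern secondary or exploratory questions. A reader might infer that the primary comparison is at risk. It is not: eHLQ by the general rule is a baseline covariate, and TAQ-NL is in no model.

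**What to change.** 1. Add a separate exploratory model for Y-BOCS with an eHLQ-by-treatment (by time) term, naming which of the seven eHLQ scales is used. Report the interaction with its confidence interval, state that power is limited, and leave the primary model as it is.
2. Replace the statement in {20b} with a list of these exploratory analyses.
3. Reconcile the TAQ-NL section with {18a} by stating one time point. If it stays at posttest, do not use it as an adjustment covariate. Report it descriptively in the app arm, or relate it only to later follow-up Y-BOCS adjusted for posttest Y-BOCS, bearing in mind that other care is allowed after the booster session.
4. Either list the experiential-avoidance subgroup question in {20b} as an exploratory interaction test or delete it from {6a}.

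The cost is wording and one or two exploratory models on data already scheduled for collection. The small downside is an interaction estimate that may be too imprecise to settle the question. Moving TAQ-NL to an earlier visit is not advised: Trial status reports 102 of 160 already included, leaving 58, or about 29 in the app arm, so its timing would be split within that arm.

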##### The eHealth Literacy Questionnaire (eHLQ)

To determine whether eHealth Literacy influences treatment effect in the intervention group, we will use the eHealth Literacy Questionnaire. The eHealth Literacy Questionnaire (eHLQ) aims to measure eHealth literacy based on the 7-dimensional eHealth Literacy Framework [41]. The eHLQ consist of 35 items that are scores on a 7-scale answers scale. It consists of 7 scales, namely; using technology to process health information, understanding of health concepts and language, ability to actively engage with digital services, feel safe and in control, motivated to engage with digital services, access to digital services that work and digital services that suit individual needs. The eHLQ was found to have good psychometric abilities [41].

### Participant timeline {13}

Figure 1 shows the participant timeline, and Fig. 2 shows the SPIRIT schedule of enrollment, interventions and assessments.

**Fig. 1 Fig1:**
[figure not shown]
Flowchart of participant timeline. In the context of parallel research goals outside the scope of this paper multiple other questionnaires not mentioned in the flowchart will be administered

**Fig. 2 Fig2:**
[figure not shown]
SPIRIT schedule of enrollment, interventions and assessments

### Sample size {14}

A statistical power analysis to estimate sample size for longitudinal, correlated data was performed [42, 43]. This analysis revealed that with an alpha of 0.05, an estimated correlation of 0.5 between measurements and a power of 0.85 the sample size needed to detect a small to medium effect (*f* = 0.35) is 160. We expect a small to medium effect since a large effect is unlikely due to the small differences between the conditions. Also, we are not interested in finding a small effect; therefore, we choose to calculate a sample size large enough to detect a clinically relevant effect with a medium effect size. Therefore, we propose a total sample size of 160 patients.

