### Outcomes {12}

#### Primary outcome measure

##### Yale-Brown Obsessive–Compulsive Scale (Y-BOCS)

Primary outcome is a decrease in symptom severity, measured with the Y-BOCS, between the measurements taken at baseline and at posttest.

The Y-BOCS is a semi-structured clinical interview which assesses the severity of obsessions and compulsions separately and is the gold standard to measure OCD severity in clinical practice and scientific research. The Y-BOCS consists of 10 items which are rated on a 4-point Likert scale. The internal consistency and validity of the Y-BOCS have proven to be good. Moreover, the Y-BOCS is sensitive to change. The Y – BOCS has been validated in a Dutch clinical population [30]. The Y-BOCS will be administered at each assessment moment by telephone by trained outcome assessors.

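### The sample size statement is internally inconsistent: f = 0.35 is not small to medium and does not lead to 160, and if 0.35 is d, the 85% power does not belong to the baseline-to-posttest outcome

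*Protocol article*

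**What the plan says.** Sample size {14} describes a power analysis for longitudinal, correlated data. With an alpha of 0.05, it gives the inputs and the target as "an estimated correlation of 0.5 between measurements and a power of 0.85 the sample size needed to detect a small to medium effect", and the result as "the sample size needed to detect a small to medium effect (*f* = 0.35) is 160". The section then explains the choice of effect: "We expect a small to medium effect since a large effect is unlikely due to the small differences between the conditions". It adds that a small effect is of no interest and that the aim is "a sample size large enough to detect a clinically relevant effect with a medium effect size". It does not state the sidedness of the test, the contrast that was powered, the number of measurements or any allowance for loss.

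The primary outcome is defined in Outcomes {12}: "Primary outcome is a decrease in symptom severity, measured with the Y-BOCS, between the measurements taken at baseline and at posttest". That is T0 to T4. Section {18a} has the primary outcome measured at all nine moments, T0 to T8, and Sequence generation {16a} gives 1:1 allocation.

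**The concern.** The section gives an effect size, a verbal label for it, a sample size and a power. If the effect size is taken as printed, neither the label nor the sample size follows from it. If 0.35 is instead a standardised difference wrongly marked as f, the label makes sense and 160 can roughly be traced. The calculation then belongs to a contrast that uses every visit to one year, not to the declared outcome.

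Readers of a null result will go to this section to see which effects the trial could have detected. As printed, it tells them that a small to medium effect had 85% power, and for the baseline-to-posttest outcome that is not established.

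**Working it through.** **Inputs.** Alpha 0.05, power 0.85, correlation 0.5 and total N 160 come from {14}; 80 per arm follows from the 1:1 ratio in {16a}. Two-sided testing, compound symmetry and no dropout are assumptions, because the article does not state them.

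**Effect-size scale.** For two equal arms f = d/2, so f = 0.35 means d = 0.70. Against the usual benchmarks for f (medium 0.25, large 0.40) this is medium to large. A value of d = 0.35, by contrast, lies below the usual medium of d = 0.5 and would fit the label.

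**Formula.** N = 4(z₀.₉₇₅ + z₀.₈₅)² v / d², with (1.960 + 1.036)² = 8.978 and 4 × 8.978 = 35.91. The variance factor v is:
- change score: 2(1 − ρ) = 1.0
- baseline-adjusted posttest: 1 − ρ² = 0.75
- mean of m visits: (1 + (m − 1)ρ)/m, which is 0.60 for m = 5 and 0.556 for m = 9

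For d = 0.70, 35.91/0.49 = 73.3. For d = 0.35, 35.91/0.1225 = 293.2. Each is multiplied by v. The table gives the normal approximation, then the noncentral t result rounded up to equal arms.

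| Contrast | N if d = 0.70 (f = 0.35) | N if d = 0.35 | Power at N = 160, d = 0.35 (t) |
|---|---|---|---|
| Change T0 to T4 | 73.3 / 76 | 293.2 / 296 | 59.5% |
| Baseline-adjusted T4 | 55.0 / 58 | 219.9 / 222 | 71.9% |
| Mean of 5 visits | 44.0 / 46 | 175.9 / 178 | 81.1% |
| Mean of 9 visits | 40.7 / 44 | 162.9 / 166 | 83.9% |

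**Reproducing 160.** No row with f = 0.35 comes near it. Repeated-measures within-between calculations at f = 0.35 need even fewer patients (22 for two measurements, down to 10 for nine). At f = 0.35 and N = 160, power is above 99% throughout. The closest match in the table is d = 0.35 averaged over all nine assessments: 163 to 166 patients, 84% power.

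**Power for the declared outcome if 0.35 is d.** Normal approximation:
- change: 0.35 × √(160/4) − 1.960 = 0.254, or 60.0%
- baseline-adjusted: 0.35 × √(160/(4 × 0.75)) − 1.960 = 0.596, or 72.4%

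The t-based values are 59.5% and 71.9%. A one-sided test gives about 71% and 82%, still below 85%.

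**What 160 patients can detect.** At 85% power, d = 2.996 × √(4v/160) = 0.474 (change) or 0.410 (adjusted). The t-based values are 0.477 and 0.413. For d = 0.5, t-based power is 88% (change) or 95% (adjusted).

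**Dropout.** The article gives no rate, so any rate is an assumption. The detectable d grows by 1/√(1 − loss):
- 10% loss: 0.477/√0.9 = 0.50 (change), 0.413/√0.9 = 0.44 (adjusted)
- 20% loss: 0.477/√0.8 = 0.53, 0.413/√0.8 = 0.46
- 30% loss: 0.477/√0.7 = 0.57, 0.413/√0.7 = 0.49

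**The case against.** The strongest reply is that 160 is adequate for the aim as worded. The section ends by sizing for a medium effect and disclaims interest in a small one. At d = 0.5 the trial has 88% to 95% power for baseline to posttest before dropout. This stands, and the corrected statement should say so.

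A second reply is that the number is traceable and that the multilevel model in {20a} uses all visits. This stands in part. It makes the likely fault a mislabelled metric and an unnamed contrast rather than an arbitrary N. Some other contrasts would do better: a baseline-adjusted mean of the four post-baseline visits up to T4, with a constant effect, has v = 0.625 − 0.25 = 0.375 and needs about 293.2 × 0.375 = 110 patients at d = 0.35. But {12} does not name that contrast.

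Three stronger readings are tempting and should be resisted:
- **That the trial has only 60% to 72% power, without qualification.** This holds only if 0.35 is d and the test is two-sided. The article prints f, and under f taken literally there is no shortfall.
- **That with f literal the trial is powered only for an effect its own text calls unlikely.** The section calls a large effect unlikely, and f = 0.35 is below the large benchmark. Under that reading the trial has over 99% power for f = 0.35 and retains 85% for much smaller effects.
- **That a linear divergence to T8 explains 160.** It does so only with nine equally spaced visits. On the actual schedule in {8} it needs about 188.

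Finally, a condensed article may leave dropout planning to the full protocol, so the missing allowance is not an error in itself.

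**Conclusion.** The point holds as an internal inconsistency in {14}, not as proof that 160 is too few. The printed f, its label, the N and the power cannot all be correct. Read literally, f = 0.35 needs at most about 76 patients in the contrasts examined, less than half of 160. Read as d, the 85% fits approximately a nine-visit average, while the outcome in {12} has about 60% (change) or 72% (baseline-adjusted) power.

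The literal result rests on the usual f = d/2 relation and the stated correlation of 0.5. The 60% and 72% also assume that 0.35 is d, a two-sided 0.05 test, compound symmetry and no dropout. The documents do not settle which reading the authors intended.

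**What to change.** Keep N = 160 and restate {14}:
- Name the effect-size metric, the sidedness, the contrast and the number of measurements, and make the contrast agree with the primary outcome in {12}.
- Remove the small to medium label from f = 0.35, or correct the metric if d was meant.
- Give the attainable figures for baseline to posttest before dropout: 85% power for d of about 0.48 on the change score, or 0.41 if the model adjusts for baseline; 88% or 95% for d = 0.5; about 60% or 72% for d = 0.35.
- Add the figures under a stated loss assumption; with 20% loss the detectable d is about 0.53 or 0.46.

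Whether to adjust for baseline is an analysis decision for the authors and should not come in through a rewording of the sample size section. The cost is a revised paragraph and, if 0.35 was meant as d, a less favourable power figure for that effect. No extra patients are needed. Trial status reports 102 participants included at the time of writing, so the statement could be corrected before the analysis.
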